#### Muscle Tension Test

We use a muscle hardness tester (OE-220 from Ito Ultra Short Wave Co, Ltd)×1 unit. Our test method is that the subject lies prone, fully exposing the skin on the waist and back, and naturally relaxes their hands, placing them on both sides of the body. Mark 8 points, which are 1.5 and 3 cun to the left and right of the L2 spinous process, and 1.5 and 3 cun left and right of the L4 spinous process. Press vertically and slowly on the surface of the measured muscle to prompt the patient to stop pressing. The obtained data will be displayed on the display screen. If the data are correct, press the record button to record the data. After 3 measurements, the display screen directly shows the average test value. The range of values is 0‐99.99, where a small value represents high muscle fiber elasticity and low muscle tension. In contrast, a significant value represents low muscle fiber elasticity and high muscle tension, expressed as a percentage of the total muscle tension. Of measurement frequency, the two groups were measured before enrollment, at week 1, at week 2, and after treatment at week 4.

#### Tenderness Score

A normal score of 0 is defined as no significant pain during heavy pressure or maximum activity.

A mild score of 1 point is defined as when under heavy pressure, the patient reports pain, but passive activity is not restricted as such.

A moderate score of 2 is defined as when under heavy pressure, the patient reports pain and frowns, indicating discomfort, with mild restricted mobility.

A severe score of 3 points is defined as when under heavy pressure, the patient reports pain and withdrawal, and passive activity is severely restricted.

For measurement frequency, the 2 groups were measured before enrollment, at week 1, at week 2, at week 4, and after treatment at week 8.

#### Adherence

At the start of this study, a group of individuals with an interest in Tuina treatment of NSLBP will be evaluated to assess their suitability for participation in the experiment. The assessment will involve collecting their medical history, conducting specialized examinations, and administering auxiliary tests under the supervision of doctors. Participants can choose whether to participate after fully understanding the grouping and procedures. Researchers will complete standardized training courses and regularly review the course videos to monitor the accuracy of the intervention measures. Before and after each treatment, a dedicated research assistant is responsible for evaluating and recording data, which is recorded in the case report form (CRF). Any exceptional circumstances that arise during treatment should be promptly reported to the Tuina doctor and documented in the CRF.

#### Safety Evaluation

The category and severity of adverse events (AEs) after each intervention are recorded in detail on the CRF, including drug allergies, subcutaneous bleeding, joint injuries, hypertension, headache, dizziness, tinnitus, fever, and other relevant conditions. The incidence of AEs will be reported as the proportion of AEs to the total number of treatments. If the AE does not improve after sufficient rest, participants should receive timely medical treatment. Suppose a serious AE occurs, the chief investigator and the ethics committee will be well-informed within 24 hours of the event. They will be knowledgeable for additional assessment and treatment and decide whether to terminate the trial. Researchers also continue to monitor patients who have experienced AE until the issue is settled, especially individuals who withdrew due to AE. If AE is proven to be related to the intervention measures in this study, participants will receive appropriate medical and economic compensation.

The medicated oil used in this study contains ingredients with known warming or irritant properties (methyl salicylate, menthol, and processed *Aconitum* species). A multilevel monitoring strategy has been implemented to ensure participant safety. First, FEMO is a government-approved proprietary Chinese medicine manufactured under good manufacturing practice standards, with strict control of potentially toxic constituents, and is approved exclusively for external use.

During each treatment session, participants are actively observed by trained Tuina physicians for any signs of abnormal local skin reactions (excessive erythema, burning sensation, pain, or discomfort at the application site). The observations are systematically documented using tenderness scores, muscle tension tests, and structured patient feedback and are collected at predefined time points.

Infrared thermal imaging is used as an objective tool to monitor local skin temperature changes. Moderate temperature elevation is considered a physiological response reflecting improved microcirculation; disproportionate or excessive temperature increases may indicate abnormal inflammatory or irritant responses.

All AEs, particularly skin-related reactions, are recorded in detail after each intervention. Participants are instructed to report any discomfort immediately. If adverse reactions occur, appropriate medical evaluation and intervention are initiated, and events are followed until resolution. Serious AEs are reported to the principal investigator and ethics committee within 24 hours, in accordance with the predefined safety management protocol.

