**Methods:**

One hundred participants will be enrolled and randomly allocated to either a TNO group (n=50) or a Tuina combined water group (n=50). Treatment will last for 4 weeks, with sessions 3 times a week, followed by a 4-week follow-up. The visual analog scale score is the primary outcome; secondary outcomes include the evaluation of treatment Japanese Orthopaedic Association scores, infrared thermography, muscle tension tests, and tenderness scores. All adverse reactions will be recorded.

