### Observation Group (TNO Group)

The dedicated attending physician of the Tuina Department is responsible for the treatment of Tuina. Tuina doctors have graduated from the Tuina College of Shanghai University of TCM, majoring in acupuncture, moxibustion, and Tuina, and have been occupied with clinical Tuina work for 5‐8 years. We finished standardized training on the techniques before treatment begins and ensured patients are treated only after passing the assessment. According to the diagnostic and treatment standards, the Tuina techniques established by the expert group will be used for intervention. The specific plan is as follows:

Rubbing tendons is applied to the paraspinal erector spinae muscle of the lumbar spine using the palm root kneading method. Up and down reciprocating operation is performed in 3 minutes. Apply, in 3 minutes, the thumb Tuina method to the attachment area of the iliac crest muscle, the affected buttocks, popliteal fossa, and calf, focusing on the areas where the patient feels sore and swollen.Apply the thumb folding finger flicking technique to the lumbar quadratus muscle, transverse process of the third lumbar vertebra, and Ashi acupoint (tenderness point or local cord-like or nodular area), with 3‐5 flicks per area, reaching the affected area. To loosen adhesions and relieve spasms for 2 minutes.Grab the affected buttocks and calf muscles for 2 minutes.The patient is advised to take a standing position and perform extreme movements such as waist flexion, lateral flexion to the left and right, and forward flexion to the left and right for 2 minutes. This is to stretch the muscles in the lower back.The patient is prone when using medicated oil for external rubbing. According to the instructions, take 8‐10 drops of the medicated oil. First, apply the medicated oil evenly to the affected area using the palm-rubbing method, and then take 6‐8 drops of the medicated oil. Use the palm rubbing method to horizontally rub the lumbar and sacral areas and vertically rub the Du meridian and foot sun meridian tendons, each about 5‐7 times, with a degree of heat transmission. At the pain point, use techniques combined with activating meridian oil to perform Tuina and pluck for 8 minutes.

The treatment frequency is 3 times a week, for 20 minutes each time.

The treatment cycle is for 4 weeks, with a total of 12 treatments. The specific action characteristics are shown in Figures 3A-3E.

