### Control Group (TNW Group)

Using the Tuina technique in the above plan, we performed step 5. When we applied the medicated oil externally, we replaced the medicated oil with clean water to form a control.

The treatment frequency was 3 times a week, for 20 minutes each time. The treatment cycle was 4 weeks.

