#### Analysis of Secondary Outcomes

Refer to the primary outcome analysis and conduct a secondary analysis of the outcomes. We will test the interarm differences for each specified end point. AE analysis was performed using the chi-square or Fisher exact test.

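### The only adverse-event incidence defined is events per treatment session, which can understate the share of participants affected by up to 12-fold; the unit of the AE test is not named

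*Protocol article*

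**What the plan says.** Safety Evaluation in the protocol article defines the summary measure: "The incidence of AEs will be reported as the proportion of AEs to the total number of treatments". It also sets how events are captured: "The category and severity of adverse events (AEs) after each intervention are recorded in detail on the CRF".

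The number of treatments comes from the intervention sections. For the oil arm: "The treatment frequency is 3 times a week, for 20 minutes each time" and "The treatment cycle is for 4 weeks, with a total of 12 treatments". For the water arm: "The treatment frequency was 3 times a week, for 20 minutes each time", again over a 4-week cycle. The abstract gives the arm sizes: "randomly allocated to either a TNO group (n=50) or a Tuina combined water group (n=50".

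On the comparison between arms, Analysis of Secondary Outcomes says only: "AE analysis was performed using the chi-square or Fisher exact test". It does not say whether participants, sessions or events enter the table. The article nowhere defines the number or percentage of participants with at least one AE.

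**The concern.** A reader of a safety report wants to know what share of patients had a reaction. The planned figure answers a different question: how many events occurred per session delivered. Because it is labelled incidence, it is easily taken for patient risk, and it will usually look much smaller.

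This matters here because safety is a stated aim alongside efficacy (Objective), and Safety Evaluation itself says that the oil contains ingredients with irritant properties. Local skin reactions are therefore the expected kind of event, and they could recur in the same person.

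The second issue is the test. Chi-square and Fisher tests need independent units, each classified once. Up to 12 sessions from one participant are not independent if some people react repeatedly, and a session with two AEs would count twice in the numerator. Whether this harms the comparison depends on which unit is tested, and the article leaves that open.

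**Working it through.** **Inputs.** 3 sessions a week for 4 weeks (both intervention sections); 50 participants per arm (abstract); two-sided alpha 0.05 (Statistical Analysis). The article gives no AE rate and no within-participant correlation, so every such value below is an assumption.

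**Denominator.** 3 × 4 = 12 sessions, which reproduces the stated total of 12. At full attendance, 50 × 12 = 600 sessions per arm and 1,200 in all.

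**Dilution.** Let k participants be affected in an arm, with m AEs each on average. The participant-level figure is k/50 and the planned figure is km/600. Their ratio is (k/50)/(km/600) = 12/m.

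- m = 1, k = 8: 8/50 = 16% against 8/600 = 1.3%, a ratio of 12.
- m = 6, k = 5: 5/50 = 10% against 30/600 = 5%, a ratio of 2.
- m = 12, k = 5: 5/50 = 10% against 60/600 = 10%, a ratio of 1.

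Since m is at least 1, 12 is the ceiling. If sessions were independent with risk p, the participant-level risk would be 1 − (1 − p)^12. For p = 1%, 2% and 5% this is 11.4%, 21.5% and 46.0%, or 11.4, 10.8 and 9.2 times p.

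**Type I error, if sessions are the unit tested.** The design effect is DE = 1 + (12 − 1) × ICC. The naive test on 600 v 600 sessions then has a true level of about 2 × [1 − Φ(1.96/√DE)]. A beta-binomial simulation checked this (50 participants × 12 sessions per arm, 20,000 trials, no true difference, assumed session risks of 2%, 5% and 10%, each session counted as AE or no AE).

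| Assumed ICC | DE | Formula | Simulation |
|---|---|---|---|
| 0 | 1.00 | 5.0% | 4.8–5.0% |
| 0.05 | 1.55 | 11.5% | 11.0–11.5% |
| 0.10 | 2.10 | 17.6% | 16.9–17.6% |
| 0.20 | 3.20 | 27.3% | 27.2–27.6% |
| 0.30 | 4.30 | 34.5% | 34.6–34.8% |
| 0.50 | 6.50 | 44.2% | 44.3–46.4% |

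Fisher's exact test on participants has 5% as an upper bound.

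**Two worked tables (Fisher exact p).**

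- Affected participants 8 v 2, one AE each: p = 0.092 by participant (8/50 v 2/50) and 0.108 by session (8/600 v 2/600). The risk ratio is 4 either way.
- Affected participants 5 v 2, each reacting at 6 sessions: p = 0.44 by participant (5/50 v 2/50) and 0.007 by session (30/600 v 12/600).

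**The case against.** The strongest reply concerns the test. A reader might infer that the planned between-arm p value is invalid. The article does not support that as a flat statement. The definition of incidence says how AEs will be reported; the sentence on testing stands in another section and names no unit. Fisher's test on participants with an AE, 50 v 50, would be ordinary and valid, and the unit may be set in a fuller document that is not shown. This stands, so the clustering argument can only be conditional. It keeps some force because the per-session figure is the only AE incidence defined, which makes it the natural quantity for the test.

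The two harms also do not peak together. Dilution reaches 12-fold only when nobody reacts twice, and then the test barely moves (0.092 v 0.108). Type I error inflates only when the same people react repeatedly, and then dilution shrinks. This stands too: the 16% v 1.3% example and the 18–34% error rates describe different situations.

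With equal attendance and one AE per affected participant, both arms shrink by the same factor, so the ratio between arms is unharmed. The damage is to the absolute figure.

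One might add that participants who stop early supply fewer sessions. That is no error in a rate per exposure, where the denominator is meant to follow treatment actually delivered.

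Finally, AEs are outside the hierarchical testing sequence and no AE comparison is powered, so the efficacy conclusion is untouched. That limits the severity but does not rescue the reported incidence.

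**Conclusion.** The point holds in a limited form. The article commits to a per-session event rate as its only AE incidence, and that rate understates the share of participants affected by up to 12-fold. This part rests on the article's own text and arithmetic, with full attendance assumed; 12 is a maximum, not an expected value.

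The effect on the test is conditional. If sessions or events enter the chi-square or Fisher table, the type I error is about 18% at an ICC of 0.1 and 34% at 0.3. Both correlations are assumptions, and the range from 0.05 to 0.5 runs from about 11% to 46%. If participants are the unit, there is no such inflation.

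This should be fixed before analysis. It does not threaten the primary result.

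**What to change.** In Safety Evaluation, define AE incidence as the number and percentage of participants with at least one AE, and with at least one skin reaction, per arm. In Analysis of Secondary Outcomes, state that Fisher's exact test is applied to participants, and give a 95% CI for the risk difference. Keep AEs per session as a descriptive rate, labelled as such. If that rate is tested, use a method that clusters by participant; the article already plans generalized estimating equations for its responder analyses.

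The cost is wording. AEs are already recorded on the CRF, and the article reports that formal analysis has not started. The one downside for the trial team is that the stated AE percentages will look larger.

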#### Quality Control

Quality control will be conducted under the guidance of an independent oversight committee to eradicate potential biases and guarantee the quality of the experiment. The steering committee comprises investigators with expertise in Tuina trials, statistical design, medication, and AEs. They are accountable for monitoring data, identifying issues, reviewing collected data, and controlling biases. The protocol will remain unchanged during the 8-week treatment period, to ensure consistency in delivery.

All physicians and evaluators are required to complete standard training. Additionally, experienced Tuina physicians will be required to complete standard training courses with nationwide recognized academic experts who have 5‐8 years of clinical experience in Tuina before the trial commences. The treatment plan should strictly follow the protocol of Tuina treatment steps, including the selection of Tuina techniques, intensity, time, sequence, and NSLBP protection measures.

Randomly assign to 2 groups simultaneously to avoid differences in the degree of NSLBP due to treatment physician and allocation bias. Participants need to cooperate in completing the entire treatment plan and follow-up.

#### Data Collecting and Monitoring

Clinical trial data will be obtained through CRFs, paper questionnaires, or online data collection applications and stored securely. Confidentiality will be maintained by assigning an encrypted numerical code to each individual. The accuracy of data input has been double-checked. The data will be locked and analyzed by 2 statisticians under the supervision of a third statistician and administrator. Then, record this trial’s data on the subwebsite of the Chinese Clinical Trial Center [34], the electronic data management system. After the data input is completed, the electronic database will be closed. Management personnel must report weekly to the steering committee on the progress of data monitoring, including the accuracy and reliability of the data. Experimental audits encompass regular, independent reviews of core experimental processes and documents, including data and scheduling monitoring, to ensure the integrity of experimental results. Data monitoring is the responsibility of the Research Department at Shanghai Municipal Hospital of TCM. The supervisor will verify that all AEs are recorded in the correct format and that they are consistent with the protocol definition. Monitoring personnel will verify the following variables for all patients: name abbreviation, date of birth, gender, signed informed consent form, eligibility criteria, randomization date, treatment allocation, AEs, and end point. The arrangement of monitoring visits will depend on the patient’s registration status, the site’s status, and other commitments. Investigators must meet with monitors at all times. If problems are discovered during the visit (ie, insufficient personnel for research and lack of research documents), the supervisor will assist in resolving the problem on-site. We will access electronic monitoring to review source files and confirm AEs.

#### Statistical Analysis

Although the sample size calculation was based on a simplified between-group comparison at the primary postintervention time point (wk 4), the primary outcome analysis will use a longitudinal modeling framework to account for repeated measurements appropriately. A linear mixed-effects model will be used, including fixed effects for treatment group, time, and group-by-time interaction, with a random intercept specified for each participant. An unstructured covariance matrix will be prespecified to model within-subject correlations across repeated VAS measurements (baseline, and wk 1, 2, 4, and 8). Sensitivity analyses using alternative covariance structures, including first-order autoregressive and compound symmetry matrices, will be conducted to assess the robustness of the results. The data analysis was performed using SPSS (version 27.0) statistical software, and the testing criteria were as follows: *α*=.05, with *P*<.05 considered statistically significant.

Given the longitudinal design with repeated measurements collected at 5 time points (baseline, and wk 1, 2, 4, and 8), all primary and secondary continuous outcomes will be analyzed rather than with independent *t* tests or simple ANOVA, which accounts for within-subject correlation and avoids violations of the independence and sphericity assumptions inherent in traditional methods.

In each linear mixed-effects model, fixed effects will include treatment group (TNO vs TNW), time (modeled as a categorical variable), and the group-by-time interaction, with a random intercept specified for each participant. An unstructured covariance matrix will be prespecified for the repeated measures, with sensitivity analyses using alternative covariance structures (autoregressive and compound symmetry) to assess robustness. The primary estimand is the between-group difference in change from baseline to week 4 (end of treatment), which is defined a priori as the primary time point based on the sample size calculation.

To control multiplicity, a hierarchical testing strategy will be applied. The primary end point (change in VAS from baseline to wk 4) will be tested at a 2-sided α level of .05. Secondary outcomes (JOA score, tenderness score, muscle tension, and infrared thermography) will be tested sequentially only if the preceding end point reaches statistical significance, thereby controlling the family-wise error rate. Longitudinal group-by-time interactions across all postbaseline time points will be considered exploratory.

Clinically meaningful improvement will be evaluated using responder analyses in addition to continuous outcomes. A reduction of ≥2 points on the VAS and an improvement of ≥4 points on the JOA score will be defined a priori as the minimal clinically significant difference. The proportions of responders will be compared between groups using generalized estimating equations, with effect sizes reported as risk ratios and 95% CIs.

#### Analysis of the Primary Outcome

The primary outcomes will be evaluated at baseline, intervention 1 week, 2 weeks, 4 weeks, and follow-up. We will conduct a sensitivity analysis on missing data (intention-to-treat analysis). The primary end point is the average change in the VAS scale from baseline to week 4 (primary end point) and week 8 (durability assessment). The baseline covariates include height, gender, age, cardiovascular history, and weight. The entire outcome scale will be measured at baseline. When the distribution is normal, nonpaired *t* tests are used to compare 2 groups, and 1-way ANOVA and repeated measures ANOVA are used to compare multiple groups. Sensitivity analysis using multiple input techniques (chain equation inputs) will be included to evaluate the impact of missing data on the main results. In addition, we will compare participants randomly assigned to the TNO and TNW groups, who received treatment considered to have high fidelity allocation. The percentage of missing data is 20%, and 5 input datasets will be used for analysis, which is the recommended minimum quantity. Before conducting any analysis, investigate any missing data patterns, identify the reasons for the missing data, and investigate the patterns to determine the validity of the hypothesis.

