### Sample Size Calculation

Based on the preliminary experimental research results, the sample size was estimated, and G*Power (version 3.1; Heinrich-Heine-Universität Düsseldorf) software was used to calculate the sample size for each group. The sample size was calculated to detect a between-group difference in the change in visual analog scale (VAS) score from baseline to week 4 (end of treatment), based on pilot posttreatment data. No power calculations were performed for week 8 outcomes, which are considered exploratory.

For grasp 1, the testing level was set at *α*=.05 and *β*=.95, and the required sample size was calculated to be 42 per group, considering a 10% dropout rate. According to 1:1 parallel grouping, VAS’s mean for the 2 pre-experimental groups was 3.57 (SD 1.35) in the TNO group and 2.61 (SD 1.39) in the TNW group. Using the above parameters, 50 patients with NSLBP should be included in each of the 2 groups, yielding a mean difference of 0.96 and a pooled SD of 1.37 (corresponding to a Cohen *d* effect size of 0.70), indicating a moderate-to-large treatment effect. The high statistical power was chosen to ensure robust internal validity, particularly given the modest, single-center study design and potential overestimation of the effect size from pilot data.

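### The sample size allows for 10% dropout, the primary-outcome analysis states 20% missing data, and the protocol does not reconcile the two figures.

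*Protocol article*

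**What the plan says.** Two sections of the protocol article give a loss figure relevant to the VAS primary outcome.

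- **Sample Size Calculation.** The calculation targets the between-group difference in VAS change from baseline to week 4. It states that "the testing level was set at *α*=.05 and *β*=.95" and that "the required sample size was calculated to be 42 per group, considering a 10% dropout rate". It then plans 50 per group, "yielding a mean difference of 0.96 and a pooled SD of 1.37" ("corresponding to a Cohen *d* effect size of 0.70"). It does not explain the step from 42 to 50.
- **Analysis of the Primary Outcome.** After naming chained-equation multiple imputation as a sensitivity analysis, it says "The percentage of missing data is 20%, and 5 input datasets will be used for analysis" and calls five the recommended minimum. It does not say whether the 20% refers to participants or VAS values, to week 4 or all visits, or to an expectation or a condition.

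The Statistical Analysis section says the primary endpoint "will be tested at a 2-sided α level of .05" and makes a linear mixed model the primary analysis. The Results section says data collection continues and formal analysis has not begun.

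**The concern.** The two percentages differ by a factor of two, both bear on the same outcome, and neither section mentions the other. Because formal analysis had not begun, nothing in the text supports reading the 20% as an observed rate. It is either a planning assumption that disagrees with the one used for sizing, or a poorly worded condition for imputation.

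What is at stake is the power claim. The protocol stresses that high power was chosen deliberately, partly because the pilot effect may be overestimated. If the analysis section's figure is the real expectation for week 4, the stated .95 does not describe the trial as planned.

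**Working it through.** **Inputs**

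- Difference 0.96, pooled SD 1.37 (Sample Size Calculation): d = 0.96/1.37 = 0.70.
- α = .05. The printed β = .95 is read here as power .95.
- 1:1 allocation, 50 randomised per group (Sample Size Calculation).
- Two-sided test (Statistical Analysis). The Sample Size Calculation gives no sidedness.
- Loss: 10% (Sample Size Calculation) or 20% (Analysis of the Primary Outcome).

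**Method.** Power of a two-sample t test from the noncentral t distribution, with 2n − 2 degrees of freedom and noncentrality d × √(n/2), where n is the number with data per group.

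**Step 1: reproduce the planned size.** At d = 0.70, α = .05 and power .95:

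- One-sided: 45 per group, and 45/(1 − 0.10) = 50. This matches the planned number.
- Two-sided: 54 to 55 per group (depending on rounding of d), or 60 to 62 after 10% loss. This does not match.
- The printed 42 does not reproduce at power .95 under either test, with or without the 10%.

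So the one route found to 50 uses 10% loss. The 45 is a back-calculation; the protocol does not print it.

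**Step 2: numbers with week 4 data, if each loss figure applies to that visit in each group.**

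- 10%: 50 × 0.90 = 45
- 20%: 50 × 0.80 = 40

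**Step 3: power at d = 0.96/1.37.**

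| Loss | n per group | Noncentrality | Two-sided .05 | One-sided .05 |
|---|---|---|---|---|
| 10% | 45 | 0.7007 × √22.5 = 3.32 | 90.8% | 95.1% |
| 20% | 40 | 0.7007 × √20 = 3.13 | 87.2% | 92.8% |

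A normal approximation agrees closely. For d = 0.70, two-sided, Φ(0.70 × √22.5 − 1.96) = Φ(1.36) = 91.3% and Φ(0.70 × √20 − 1.96) = Φ(1.17) = 87.9%.

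**Step 4: separate the two sources of shortfall.** Moving from 10% to 20% loss costs 90.8 − 87.2 = 3.6 points two-sided, or 95.1 − 92.8 = 2.3 points one-sided. Moving from a one-sided to a two-sided test costs 95.1 − 90.8 = 4.3 points at 10% loss, or 92.8 − 87.2 = 5.6 points at 20% loss. In either order, sidedness accounts for more of the gap to .95 than the loss figure does.

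**Step 5: how much loss 50 per group covers if the printed 42 is taken at face value.**

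- If 42 is the number needed with data, 50 covers (50 − 42)/50 = 16% loss, which is less than 20%.
- If 42 already includes the 10%, about 42 × 0.90 = 38 are needed with data, and 50 covers (50 − 38)/50 = 24%, which is more than 20%.

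The text does not say which is meant.

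**The case against.** The strongest reply is that the two figures may not measure the same thing. Dropout is a share of participants in a week 4 calculation. The missing-data percentage sits in a section covering five assessments, including week 8, and in a sentence about the number of imputed datasets. A 10% dropout with some intermittent and week 8 gaps could give 20% missing values overall, or the sentence may be a garbled condition for using five imputations. This stands: the power figures for 40 per group hold only if the 20% applies to week 4. But the protocol offers none of these explanations, so the sentence needs correcting on any reading.

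A second reply is that 50 exceeds 42 and so leaves slack. That holds on one reading of 42 and fails on the other (step 5). As 42 does not reproduce from the stated inputs, it cannot settle the matter.

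Third, the effect is small and the primary mixed model uses participants with partial data. Both points are right, so 40 per group is a worst case under the 20% assumption.

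A reader might infer three stronger conclusions that the documents do not support:

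- **That missing data weigh twice as heavily in the primary result.** The primary analysis is the mixed model, and multiple imputation is only a sensitivity analysis, so the 20% sentence does not govern the primary estimate.
- **That 20% loss gives less power than any calculation built on 10%.** It does not. The printed 42 less 10% leaves about 38 per group and 85.4% two-sided power, below the 87.2% for 40.
- **That the trial is underpowered.** About 87% at the plan's own effect does not show that.

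**Conclusion.** The inconsistency holds: 10% in the sizing and 20% in the primary-outcome analysis, unreconciled and with the 20% undefined. If 20% is the expected week 4 loss in each group, 50 randomised per group give about 87% power two-sided (93% one-sided) at d = 0.70. The stated .95 is then not reached under either test. At 10% loss the two-sided figure is about 91%.

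These figures assume a simple two-sample comparison of week 4 change, the pilot effect taken as true, and equal loss in both groups. They are conservative for the planned mixed model. The part due to the loss figure is 2 to 4 points; the larger part of the gap comes from the two-sided test and is a separate matter. This is a correction to a stated design figure and does not call the trial's size into question.

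**What to change.** State one expected loss at week 4 and use it in both Sample Size Calculation and Analysis of the Primary Outcome. Restate the power for 50 per group at that loss under the two-sided .05 test: about 91% at 10% or about 87% at 20%, for d = 0.70 and a simple two-sample comparison.

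If the 20% was meant as a condition for imputing, replace the flat statement with that condition and base the imputation on the observed missing fraction. If it covers all visits or week 8, say so.

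The protocol reports 100 participants already enrolled, and no added enrolment is proposed. The cost is a few sentences and one recalculated figure; the downside is a less favourable stated power. The change is best made before formal analysis begins, so that the expected loss is not settled after the data are seen.
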